### Study Termination

Patients have the right to withdraw from the proposed study at any time without reason. Such withdrawal will not affect the patients’ rights to receive appropriate medical management in the future. However, researchers will terminate the study for patients having the following situations: poor adherence to the treatments; serious adverse drug reactions; pregnancy; patients refusing to continue participating in the study; lost to follow-up; or other safety reasons.

Excessively high withdrawal rates may lead to unexplained results. Therefore, unnecessary withdrawal should be avoided. Withdrawal reasons should be clarified and registered on the CRF. Researchers should evaluate, judge, and follow up on adverse events that lead to patient withdrawal. Study medications that have been assigned to withdrawing patients cannot be reassigned to other patients. Subjects who quit cannot be replaced. If a subject withdraws before the end of the study, related assessments should be performed for the subject at the end of the study.

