## Materials and Methods

### Patient and Public Involvement

This is a prospective, open-label, randomized, parallel-group, and multicenter study. We are planning to include 500 patients with acute phase ACS (non-ST-segment elevation myocardial infarction (MI), acute ST-segment elevation MI within 24h of onset, and unstable angina within 72h of onset). Patients will be randomly assigned in a 1:1 ratio using a computer-generated random number system (block randomization with blocks of size 4 at random) and are divided into two treatment groups: statin-only therapy and evolocumab plus statin therapy. A 48-week follow-up study will be conducted.

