### Main Outcome Measures

Subjects of the present study will receive 24 treatments after being enrolled, and data of laboratory examinations will be evaluated at 72h and weeks 1, 4, 8, 12, 24, and 48 after intervention (Table 1; Figure 1).

The primary outcome of the present study will be the mean percentage change of the LDL-C level between baseline and weeks 4 and 12 post-treatment (Table 1; Figure 1). The secondary outcome will be MACE (defined as coronary heart disease death, nonfatal myocardial infarction, hospitalization for unstable angina, unplanned coronary revascularization, and stroke) assessed at week 12 and week 48 post-treatment (Table 1; Figure 1). The following issues will also be investigated: (1) the proportion of patients with LDL-C<70mg/dl, <55mg/dl and<40mg/dl during the study period; (2) patients’ quality of life as evaluated with the PROMIS 10 scale at week 12 and week 48 post-treatment; and (3) the percentage change in inflammatory biomarkers including but not limited to high-sensitivity C-reactive protein (hsCRP), interleukin (IL)-1β and IL-6, from baseline to weeks 48 (Table 1; Figure 1). Other biomarkers that exhibit significant difference between the two study arms will be investigated retrospectively after the trial.

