### Statistical Analysis

The primary efficacy analysis will be based on the time from randomization assignment to the first occurrence of any component of MACE. Data will be analyzed using intention-to-treat analysis (ITT) and per protocol (PP) to assess the efficacy and safety of evolocumab in combination with moderate-intensity statin therapy. The superiority of evolocumab will be assessed for all efficacy endpoint. Continuous variables with an approximately normal distribution will be reported with mean±standard deviation (mean±SD), and differences between the two treatment arms will be tested using independent sample t-test. For continuous variables that are not normally distributed, the median and interquartile range (IQR) will be given, and the nonparametric Mann–Whiney U test will be conducted to test for differences between treatment arms. Discrete variables will be reported with counts and percentage for each arm, and differences between arms will be examined using Fisher’s exact test. In order to compare MACE differences, Kaplan–Meier survival curve analysis will be performed, and hazard ratio (HR) and 95% CI will be calculated. Log-rank tests will also be performed to evaluate the differences in significance and verify treatment efficacy.

The ITT population will include all randomized patients and the PP population will include all randomized patients who complete the entire study. Subjects with missing data will be excluded from the corresponding analysis. Logistic regression will be used to analyze differences in the central effect sizes.

Results of the proposed study will be analyzed using SAS 9.2 or higher version (SAS Institute, North Carolina, United States) software. All statistical tests will be two-tailed unless otherwise indicated or presented with a 95% confidence interval (CI), and statistical significance will be established as *p*<0.05.

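### Study Termination does not separate stopping study drug from leaving follow-up, so outcomes needed for the all-randomized analysis are not secured in terminated patients

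*Protocol article*

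**What the plan says.** Study Termination in the protocol article first gives patients the right to withdraw. It then sets a rule for the researchers: "researchers will terminate the study for patients having the following situations: poor adherence to the treatments; serious adverse drug reactions; pregnancy". The list ends with "patients refusing to continue participating in the study; lost to follow-up; or other safety reasons". What ends is the study for that patient. The section does not describe a patient who is off study drug and still followed.

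Two sentences in the same section govern what is collected afterwards: "Researchers should evaluate, judge, and follow up on adverse events that lead to patient withdrawal", and "If a subject withdraws before the end of the study, related assessments should be performed for the subject at the end of the study". The second does not say which assessments are meant, or whether the end of the study is the patient's exit or week 48.

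Main Outcome Measures sets the LDL-C outcome at weeks 4 and 12 and has MACE "assessed at week 12 and week 48 post-treatment". Statistical Analysis says that "The ITT population will include all randomized patients", analyses time from randomization to first MACE, defines the per-protocol set as those who finish the whole study, and leaves subjects with missing data out of the affected analysis. Safety Evaluation does not impute missing safety data.

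**The concern.** An analysis of all randomized patients needs outcomes from everyone, including those who adhere poorly or react to the drug. The termination rule removes those patients from the study for reasons tied to treatment and probably to prognosis. If their outcomes are then not collected, they leave the per-protocol set by definition, and they leave the intention-to-treat analysis wherever a value is missing. The two populations drift together.

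For MACE, the risk is informative censoring, or outright exclusion if the missing-data sentence is applied literally. For LDL-C, the comparison loses patients terminated before week 4 or week 12. For safety, harms that first appear after termination may go unrecorded.

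The arms may also be affected differently. The article states: "This is a prospective, open-label, randomized, parallel-group, and multicenter study". Both arms take a daily statin, but only one also has 24 injection time points. That arm has a second treatment to miss or react to, and those deciding on termination know the allocation.

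**Working it through.** **1. The plan's own drop-out figure.** Sample Size Calculation gives 193 per arm and 20% drop-out: 193 / (1 − 0.20) = 241.25, rounded up to 242 per arm and 484 in total, then raised to 500. This reproduces. Twenty percent of 500 is 100 patients, 50 per arm. That allowance covers all drop-out and is not split by reason or arm, so it does not measure researcher-imposed termination.

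**2. What the analysis needs against what the text secures after termination.**

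| Outcome | Needed | If the final assessment is at exit | If it is at week 48 |
|---|---|---|---|
| LDL-C | Weeks 4 and 12 | Only if exit happens to fall on that week | Not obtained if terminated earlier |
| MACE | Dated events to week 48 | Nothing secured after exit | Recoverable in retrospect, but MACE is not named |
| New adverse events | To week 48 | Nothing secured after exit | Not named; only the event that led to withdrawal is followed |

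Neither reading secures all three. The LDL-C loss arises only for patients terminated before the week in question. Its size cannot be derived, because the article gives no LDL-C effect size or standard deviation.

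**3. Illustration for MACE. The termination shares and risk multiples are assumed.** Suppose there is no true effect, so the overall 48-week risk p is the same in both arms. In an arm, a share d is terminated, and these patients have k times the risk r of those who stay. Terminated patients are excluded from the analysis.

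- p = (1 − d)·r + d·k·r, so the observed risk is r = p / [1 + d(k − 1)].
- Observed ratio, evolocumab (E) to statin only (S): [1 + d_S(k − 1)] / [1 + d_E(k − 1)]. The overall risk p cancels.

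| Terminated, E vs S | k = 1 | k = 2 | k = 3 |
|---|---|---|---|
| 20% vs 20% | 1.00 | 1.20/1.20 = 1.00 | 1.40/1.40 = 1.00 |
| 25% vs 15% | 1.00 | 1.15/1.25 = 0.92 | 1.30/1.50 = 0.87 |
| 15% vs 25% | 1.00 | 1.25/1.15 = 1.09 | 1.50/1.30 = 1.15 |
| 30% vs 10% | 1.00 | 1.10/1.30 = 0.85 | 1.20/1.60 = 0.75 |
| 10% vs 30% | 1.00 | 1.30/1.10 = 1.18 | 1.60/1.20 = 1.33 |

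Full exclusion is the severe end. Patients censored part-way contribute time before termination, and the distortion shrinks accordingly.

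**4. Events lost with equal termination.** Assume 12% risk and 250 per arm, which gives 30 events. With d = 0.20 and k = 2, r = 12% / 1.2 = 10%, and the 50 terminated patients have 20% risk. That is 50 × 0.20 = 10 of 30 events lost if they leave near the start, and about 5 if they leave half-way.

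**The case against.** The strongest reply is that the article does not cut follow-up off. Adverse events leading to withdrawal are pursued, and a withdrawn subject is assessed at study end. Taken literally, that is a late contact, and death, infarction, revascularization, hospitalization and stroke can all be dated in retrospect. This stands. A reader might infer that follow-up simply stops, or that the data will not exist and no analysis could recover the comparison. The text does not support that; it leaves the matter undefined.

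Second, no section gives or assumes termination rates by arm. Control patients who know that they are not receiving the study drug might leave more often, which reverses the direction. This also stands: unequal loss is a plausible risk, not a stated fact. A reader might take 20% terminated on evolocumab and none on control, with 3 times the risk, and obtain 1/1.4 = 0.71. The arithmetic is right, but the documents do not support that split.

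Third, refusal and loss to follow-up can end contact under any rule, so not all of the 20% drop-out can be charged to this one.

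Fourth, this is a condensed article, and the full protocol may describe visits after stopping drug. One therefore cannot say that the trial has no such follow-up. But the point rests on a rule that the article does state, and that rule conflicts with the stated analysis.

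Fifth, the section sets no threshold for poor adherence and itself warns: "Excessively high withdrawal rates may lead to unexplained results. Therefore, unnecessary withdrawal should be avoided". That may limit how often the rule is applied, but it also shows that the authors see the danger in a rule that makes withdrawal mandatory.

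**Conclusion.** The point holds as a data-collection fault. The rule ends study participation for treatment-related reasons, and the two follow-up sentences do not secure LDL-C at weeks 4 and 12 or explicitly secure MACE and new adverse events to week 48. This is at odds with the all-randomized analysis, and the exclusion of subjects with missing data compounds it.

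Size and direction are unknown. Under the assumed 25/15 splits, the observed MACE ratio with no true effect ranges from 0.87 to 1.15. It stays at 1.00 if termination and its relation to risk are the same in both arms, or if terminated patients have the same risk as the rest. These figures show sensitivity; they do not predict what will happen in this trial. Unrecorded outcomes may not be recoverable later, and any analysis that fills the gap would rest on assumptions that the data cannot test. The sample size arithmetic is unaffected.

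**What to change.** Change data collection only:

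- State that a patient whose study treatment is stopped for any reason stays in the study for the remaining scheduled assessments: LDL-C at weeks 4 and 12, MACE at weeks 12 and 48, and adverse events to week 48. Use telephone contact or record review if the patient cannot attend. The exception is withdrawal of consent to follow-up.
- Record date and reason of stopping treatment separately from date and reason of leaving the study.
- Replace the undefined assessment at study end with these dated assessments.

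The clinical decision on when to stop treatment stays as it is.

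The cost is protocol wording and a case report form page. The lipid visits are already in Table 1, and the MACE times are already in Main Outcome Measures. Table 1 has no row for MACE or adverse events, so those contacts should be written in. The documents give no budget, so the expense cannot be stated. The small downsides are that sites keep contact with patients off drug and that the estimated effect includes off-drug time.

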### Sample Size Calculation

This is a superiority trial, and the sample size calculation is based on the primary efficacy endpoint, namely the percentage of change in LDL-C levels from baseline to week 4 after randomization. In order to have 90% power to detect clinically meaningful differences in treatment effects with a one-sided significance level of 5% (α=0.05), a sample size of 193 patients is required for each treatment arm. Assuming that the drop-out rate is 20%, this study aims to enroll approximately 484 patients, with 242 patients in the evolocumab plus statin arm and 242 in the statin-only arm. Therefore, the proposed study is expected to enroll a total of 500 patients with acute phase ACS, with 250 patients in each treatment arm.

The number of patients enrolled from each hospital is based on the bed size of each hospital. The Tianjin Chest Hospital plans to enroll 220 patients, and the remaining seven hospitals each will enroll 40 patients.

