## Abstract

**Background:** Several studies have demonstrated that using a higher dose of statin can easily induce liver injury and myopathy. Low-density lipoprotein cholesterol (LDL-C) is a well-established modifiable risk factor for cardiovascular disease; however, the large majority of Chinese patients cannot meet the target level of LDL-C recommended by the Chinese expert consensus. Evolocumab has been demonstrated to reduce LDL-C by approximately 60% in many studies. Nevertheless, whether combined evolocumab and moderate-intensity statin is as effective in lowering LDL-C and decreasing incidence of MACE in Chinese patients presenting with the acute phase of acute coronary syndrome (ACS) remains unknown. Therefore, the “Evolocumab added to Moderate-Intensity Statin therapy on LDL-C lowering and cardiovascular adverse events in patients with Acute Coronary Syndrome” (EMSIACS) is conducted.

**Methods:** The EMSIACS is a prospective, randomized, open-label, parallel-group, multicenter study involving analyzing the feasibility and efficacy of evolocumab added to moderate-intensity statin therapy on lowering LDL-C levels in adult Chinese patients hospitalized for acute phase ACS. The sample size calculation is based on the primary outcome, and 500 patients will be planned to recruit. Patients are randomized in evolocumab arm (evolocumab 140mg every 2weeks plus rosuvastatin 10mg/day or atorvastatin 20mg/day) and statin-only arm (rosuvastatin 10mg/day or atorvastatin 20mg/day). The primary outcome is the percentage change in LDL-C in weeks 4 and week 12 after treatment. The secondary outcome is the occurrence of MACE after 12weeks and 1year of treatment.

**Discussion:** If the EMSIACS trial endpoints prove statistically significant, the evolocumab added to moderate-intensity statin therapy will have the potential to effectively lower subjects’ LDL-C levels, especially for the Chinese patients with acute phase ACS. However, if the risk of MACE is not significantly different between the two groups, we may extend follow-up time for secondary outcome when the clinical trial is over.

**Clinical trial registration**: The study is registered to ClinicalTrials.gov (NCT04100434), which retrospectively registered on November 24, 2020.

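### The LDL-C sample size is set at a one-sided 5% level but the analysis rule is two-tailed at p<0.05; if both apply as written, power is about 83–85%, not 90%, after the planned drop-out

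*Protocol article*

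**What the plan says.** Under Sample Size Calculation, the protocol article describes a superiority trial sized on "the percentage of change in LDL-C levels from baseline to week 4 after randomization". The target is 90% power, and the level and the resulting number per arm are given in these words: "with a one-sided significance level of 5% (α=0.05), a sample size of 193 patients is required". With 20% drop-out this becomes 242 per arm and 484 in total, which is then raised to 500 (250 per arm). Neither the difference to be detected nor its standard deviation is printed.

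Under Statistical Analysis, the general rule is "All statistical tests will be two-tailed unless otherwise indicated". The same sentence mentions a 95% confidence interval and puts the threshold for significance at p<0.05. Continuous outcomes are compared by an independent-sample t-test, or by a Mann–Whitney test if not normally distributed, and no direction is attached to either. Subjects with missing data are left out of the corresponding analysis.

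**The concern.** The level used to size a comparison should be the level at which it is tested. Here the design section uses one-sided 5% and the analysis section defaults to two-tailed 5%, which puts only 2.5% in the favourable direction. If both statements are taken literally, the 90% power belongs to a test that will not be performed.

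Two things are at stake. One is whether the stated power is correct. The other is the threshold for claiming superiority on LDL-C: if it stays open, a one-sided p-value between 0.025 and 0.05 could be called significant under one section and not under the other. That should be settled before results are seen.

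**Working it through.** **Inputs from the protocol article.** Power 90%, one-sided 5%, 193 per arm, 20% drop-out and 250 per arm enrolled (Sample Size Calculation); two-tailed, p<0.05, t-test, missing data excluded (Statistical Analysis); 1:1 allocation (Patient and Public Involvement). Assumption: because no difference or SD is printed, the standardised difference d is back-solved from 193.

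**1. The plan's own figures.** Drop-out: 193/0.8 = 241.25, rounded up to 242 per arm, and 2 × 242 = 484. This reproduces. The figure of 193 cannot be reproduced independently without a difference and an SD.

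**2. Effect implied if 193 was sized one-sided.** d = (z₀.₉₅ + z₀.₉₀) × √(2/n) = (1.645 + 1.282) × √(2/193) = 0.298.

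**3. Power for that effect at two-sided 5%.** Power = Φ(d√(n/2) − 1.960), using unrounded d = 0.2979.

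| Evaluable per arm | d√(n/2) | Two-sided power, normal | Two-sided power, noncentral t |
|---|---|---|---|
| 193 | 2.926 | Φ(0.966) = 83.3% | 83.1% |
| 200 (250 less 20%) | 2.979 | Φ(1.019) = 84.6% | 84.4% |
| 250 (none missing) | 3.331 | Φ(1.371) = 91.5% | 91.4% |

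The fall from 90% to 83.3% at 193 does not depend on the difference and SD separately. It comes only from moving the critical value from 1.645 to 1.960.

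**4. Number needed to keep 90% at two-sided 5%.** 2 × (1.960 + 1.282)²/0.2979² gives 237 evaluable per arm. With 250 enrolled per arm, that allows 13/250 = 5.2% missing.

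**5. If 193 was in fact sized two-sided.** With d = 0.33, 2 × (3.2415/0.33)² = 192.97, which rounds up to 193. The same printed number therefore fits a two-sided 5% calculation with 90% power, at a slightly larger effect. The text cannot tell the two origins apart.

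**6. If the LDL-C test is meant to be one-sided at 5%.** Power at 193 is Φ(2.926 − 1.645) = 90%, as stated. The favourable-direction error is 5% against 2.5% under the general rule, a ratio of 2. For one-sided p between 0.025 and 0.05, superiority would be declared while a two-sided 95% CI includes zero.

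**The case against.** The strongest reply is that the general rule carries its own exception clause, and the sample size section is the one place that indicates something different. On that reading the 90% and the one-sided 5% are both correctly stated, and the design is lenient but disclosed. This reading is possible. It is not secure, because the sample size section fixes a design level and names no test, and the section that names the tests gives none a direction.

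A reader might infer that the plan's power or its error rate must be wrong however the text is read. The documents do not support that. The exception reading keeps both figures, and under a two-sided origin for 193 only the word 'one-sided' is wrong.

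The 83–85% range also depends on the 20% drop-out having nearly all occurred by week 4. Follow-up runs to 48 weeks and the article does not say when drop-out is expected, so for the back-solved effect a fair span is about 83% to 91.5%. That qualification stands.

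A reader might also set the implied 0.3 SD against the Abstract's statement that "Evolocumab has been demonstrated to reduce LDL-C by approximately 60% in many studies" and conclude that the calculation is mis-specified. That does not follow. The section sizes on a clinically meaningful difference, which may properly be smaller than the expected one, and the Abstract's figure describes other studies, not this trial's assumed between-arm difference. What the comparison does suggest is that the LDL-C result is unlikely to be at risk. For an assumed difference of 30 points with an assumed SD of 30 to 40, two-sided power at 193 per arm exceeds 99.9%.

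Finally, the unprinted difference and SD are details that an article may leave to the full protocol. Their absence is not an error here; it only means that the conflict cannot be resolved from this text.

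**Conclusion.** The point holds as a conflict between two printed statements. Which of them governs the LDL-C test cannot be settled from the article.

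- **Sized one-sided, tested two-sided:** the stated 90% is about 83% at 193 and about 85% at 200 evaluable per arm, rising to about 91.5% only with no missing data.
- **Sized and tested one-sided at 5%:** 90% stands, at twice the favourable-direction error of the general rule and with possible disagreement with a 95% CI.
- **Sized and tested two-sided (about 0.33 SD):** 90% stands and only the word 'one-sided' needs correcting.

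The first figures rest on an effect back-solved from 193, not on one the sponsor has stated, and they apply to the LDL-C comparison only. The correction is worth making because the level and direction of a primary test should be fixed in advance. It is not a threat to the trial and does not show that the LDL-C comparison is underpowered for the effect the investigators expect.

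**What to change.** State one sidedness and one alpha for the primary LDL-C test, in the same terms, in both the Sample Size Calculation and Statistical Analysis sections. Two-sided 5% (equivalently one-sided 2.5%) is preferable because it agrees with the general rule and with a 95% CI. Then restate the power on that basis, giving the assumed difference and SD:

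- If 193 was sized one-sided and about 0.298 SD is the intended effect, state power of about 85% with 200 evaluable per arm (250 enrolled, 20% drop-out).
- If 193 was sized two-sided, replace the word 'one-sided', keep 90%, and give the effect as about 0.33 SD.

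The sponsor has to say which applies; neither power figure should be inserted without that confirmation. The cost is a paragraph of wording and possibly a slightly lower stated power. Enrolment stays at 500 and trial conduct does not change.
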